### Patient satisfaction survey

A structured telephone-based patient satisfaction survey will be conducted with a sub-sample of patients. The survey is based on key performance indicators (KPIs) aligned with PHCC clinical practice guidelines for diabetes management. This tool was developed and validated by the Department of Clinical Effectiveness to ensure relevance and reliability in measuring patient experience.

Survey data will be recorded using a secure Excel spreadsheet preformatted with all measurement parameters. *(see*
Table 2
*for Patient Satisfaction Questionnaire).*

**Table 2 pone.0313664.t002:** Patient Satisfaction Survey Indicators.

Question	Indicator
Q1	Did your doctor inquire about and discuss diabetes-related signs and symptoms?
Q2	Did your doctor request any new blood tests or referrals?
Q3	Did your doctor explain how to monitor blood sugar and what to do in case of high/low readings?
Q4	Did your doctor provide advice about diet and physical activity?
Q5	Did your doctor set an HbA1c goal and discuss your treatment plan?
Q6	Overall, are you satisfied with the care provided during your visit?

Source: PHCC clinical practice guideline for the management of Type 2 Diabetes.

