### Sample selection

A stratified simple random sampling method will be employed to select representative samples for both the cross-sectional and cohort components of the study. For the cross-sectional analysis, a total of 450 patient records will be randomly selected from the medical records department across 31 health centers. This sample size was calculated based on a 5% margin of error, a 95% confidence interval, and an assumed response distribution of 50%, with an additional allowance for potential non-responses. The selection will take place at two different time points: baseline and post-intervention, with 450 cases reviewed at each stage to facilitate a comparative analysis of diabetes-related encounters over the preceding three months.

For the patient satisfaction component, a subset of 60 patients will be randomly selected at each time baseline and post-intervention—from the larger cohort. These patients will be contacted by telephone to complete satisfaction surveys, offering qualitative insights into their perceptions of care. The randomization process will be independently applied at both time points to ensure comparability and minimize selection bias. A sample size of 60 patients per time point is considered sufficient to balance feasibility with the need for meaningful analysis of patient satisfaction trends. This approach ensures the robustness and reliability of findings and supports a comprehensive evaluation of both clinical outcomes and patient perspectives throughout the intervention period.

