### Medical record review

The medical record review will be conducted by experienced clinical auditors trained in assessing adherence to evidence-based diabetes management guidelines. Data will be systematically recorded using a customized Excel spreadsheet developed specifically for this study, containing all predefined audit criteria.

The review will focus on newly diagnosed type 2 diabetes mellitus (T2DM) patients, particularly those with an HbA1c value ≥6%, to assess whether appropriate clinical services and interventions were delivered in line with guideline recommendations.

The collected data will allow a comprehensive evaluation of healthcare provider adherence, identifying gaps in clinical care and informing quality improvement initiatives across PHCC settings. *(see*
Table 1
*for data collection variables).*

**Table 1 pone.0313664.t001:** Clinical Audit Criteria and Variables.

Criterion	Description
Criterion 1	ASCVD risk assessment for all adult patients (≥40 years) at diagnosis
Criterion 2.1	Laboratory Investigations: HbA1c, lipid profile (TC, HDL, LDL, TG), serum creatinine and eGFR, liver function (ALT, AST), urine albumin/creatinine ratio, TSH (if dyslipidemia or female >50 years), urine ketones (if glucose >250 mg/dL), serum potassium (if on ACEi/ARB/diuretics)
Criterion 2.2	Initial general foot examination
Criterion 2.3	Referral to eye specialist for initial retinal assessment
Criterion 3	Documentation of HbA1c target goals
Criterion 4	Appropriate treatment initiated or adjusted based on guidelines
Criterion 5	Patient education on diet and physical activity at initial visit
Criterion 6	Referral to dietitian for Medical Nutrition Therapy (MNT)
Criterion 7	Follow-up HbA1c test ordered within 3–6 months from treatment initiation

Source: PHCC clinical practice guideline for the management of Type 2 Diabetes.

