### Intervention and follow-up

Following the initial cross-sectional analysis, identified gaps in care quality and patient satisfaction will inform the development of a comprehensive action plan. This plan will be implemented across all participating health centers to address the deficiencies and enhance service delivery. The intervention will be embedded into standard auditing procedures to ensure continuous quality improvement.

The intervention phase will last approximately 8–9 months. Afterward, a second round of data collection will be conducted using the same methodology and variables to ensure consistency and enable direct comparison. This approach will support the evaluation of changes in clinical performance and patient experience before and after the intervention *(see*
Fig 1
*for the study flow chart).*

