### Analytical plan

Data will be extracted from the electronic health record system at two separate points: one time at a point before the intervention and the other time at a point after the implementation of the intervention. Excel will be used to collect and organize the data. PivotTables will be used to determine the frequency of cases across variables. Excel will be further used to produce histograms and other figures.

Study outcome variables will be assessed using independent tests like Chi square or t test to compare between the two groups. For satisfaction, we will do it frequently by percentage P=(F/T) *100.

The statistical analysis will be performed using STATA 15.1 (College Station, TX, USA). A Wilcoxon sign rank test will be used to find the mean difference between the pre- and post-assessment. P < 0.05 will be considered statistically significant. A logical model of protocol presented in Fig 2.

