### The role of clinical audit champions

Clinical audit champions play a key role in bridging the gap between strategic planning and on-the-ground implementation. They are responsible for coordinating local efforts, monitoring compliance with action plans, and reporting progress [16–18]. In this study, clinical audit champions were instrumental in tracking implementation activities at the health center level. They maintained logs and shared periodic updates during six-weekly regional meetings organized by the clinical effectiveness team. These meetings served to track key metrics, troubleshoot challenges, and document improvements or barriers encountered during implementation.

Importantly, audit champions were authorized, in coordination with health center managers, to implement changes aligned with the approved QI plan. Changes implemented included improvements in documentation practices (e.g., timely HbA1c goal setting, foot exam documentation), adherence to referral protocols, and patient counseling activities. These modifications were monitored using structured tracking forms and validated during follow-up audits, providing clear evidence of implementation progress.

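### Survey item Q5 puts HbA1c goal-setting and treatment-plan discussion in one question, so its before-after percentage cannot isolate patient-reported goal-setting; one added item would fix this.

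*Protocol article*

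**What the plan says.** The section on the patient satisfaction survey lists six items in Table 2. Q5 reads "Did your doctor set an HbA1c goal and discuss your treatment plan". The article prints neither response options nor a scoring rule. It says that the responsible department developed and validated the tool, and shows no item-level results.

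The Analytical plan gives one summary for this component: "For satisfaction, we will do it frequently by percentage P=(F/T) *100". Sample selection sets 60 patients at each time point. Intervention and follow-up says that the gaps found at baseline, including those in patient satisfaction, will shape the action plan. It adds that the second round will be run "using the same methodology and variables to ensure consistency and enable direct comparison".

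Goal-setting also appears in two other places. The medical record review audits "Documentation of HbA1c target goals" as Criterion 3, in 450 records per round. The section on clinical audit champions names "timely HbA1c goal setting, foot exam documentation" as examples of improved documentation practice.

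**The concern.** A doctor can discuss a treatment plan without setting an HbA1c goal. A patient in that position must decide whether the *and* in Q5 requires both acts. One who takes it literally says no; one who hears a general question about the treatment talk says yes. Once recorded, a single answer cannot be divided into its parts.

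Two uses of the survey suffer:

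- **Baseline.** A low Q5 could mean that goals are not set, that plans are not discussed, or both. The action plan is meant to be built on such gaps, and Q5 does not say which one to address.
- **Before-after comparison.** A change in Q5 mixes changes in two acts, and its size depends on how respondents read the question. Repeating the same item in both rounds carries the ambiguity into the comparison.

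Q5 is the only listed survey item in which the patient reports whether a goal was set.

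**Working it through.** The protocol gives no expected rate, effect size or power for Q5, so there is no figure of its own to reproduce. The rates below are assumptions that show direction and range.

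**Inputs.** From the document: two acts in one item, a percentage summary, 60 patients per round. Assumed: goal-setting rate *g*, plan-discussion rate *t*, and how far the acts overlap.

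**Formulas.** If the acts are independent:
- *both* reading: P(yes) = g × t
- *either* reading: P(yes) = 1 − (1 − g)(1 − t)

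If a goal is only ever set within a plan discussion (nested, g ≤ t):
- *both*: P(yes) = g
- *either*: P(yes) = t

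**Case 1: goal-setting rises from 40% to 60% (20 points), plan discussion stays at 80%.**
- Independent, *both*: 0.4 × 0.8 = 32%, then 0.6 × 0.8 = 48%; rise of 16 points.
- Independent, *either*: 1 − 0.6 × 0.2 = 88%, then 1 − 0.4 × 0.2 = 92%; rise of 4 points.
- Nested, *both*: 40% to 60%; the full 20 points.
- Nested, *either*: 80% to 80%; no change shown.

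**Case 2: goal-setting flat at 40%, plan discussion rises from 60% to 90%.**
- Independent, *both*: 0.4 × 0.6 = 24%, then 0.4 × 0.9 = 36%; rise of 12 points with no change in goal-setting.
- Independent, *either*: 1 − 0.6 × 0.4 = 76%, then 1 − 0.6 × 0.1 = 94%; rise of 18 points.
- Nested, *both*: 40% to 40%; no false rise.
- Nested, *either*: 60% to 90%; rise of 30 points.

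**A second set of rates: goal-setting 30% to 60%, acts independent.** Power is for 60 per round, independent samples and two-sided 0.05 (sidedness is assumed).

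| Item or reading | Plan discussion | Recorded change | Power |
|---|---|---|---|
| Separate goal item | any | 30% to 60% (+30) | about 92% |
| *Both* | 80% | 24% to 48% (+24) | about 79% |
| *Either* | 80% | 86% to 92% (+6) | about 18% |
| *Both* | 50% | 15% to 30% (+15) | about 50% |
| *Either* | 50% | 65% to 80% (+15) | about 45% |
| *Both* | 95% | 28.5% to 57% (+28.5) | about 89% |
| *Either* | 95% | 96.5% to 98% (+1.5) | about 7% |

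**Reading alone.** With care fixed at 30% and 80%, Q5 reads 24% if everyone uses *both*, 55% if half use *either*, and 86% if everyone does.

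**Bounds.** A *both* answer can never exceed the goal-setting rate, so Q5 read strictly is a lower bound for that rate in each round. It does not bound the change between rounds, as case 2 shows.

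**The case against.** Much of the case on the other side stands.

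- **Criterion 3 measures goal-setting already.** A reader might infer that the study cannot measure this target. The documents do not support that. The section on audit champions treats goal-setting as a documentation improvement, and Criterion 3 audits that documentation as a single act in 450 records per round.
- **Yes/no coding and item-level percentages are inferred.** They follow naturally from the form of the questions and from the formula, but neither is printed. Trained interviewers may have a script or coding rule that the article omits.
- **A patient who received one act can answer no.** It would be wrong to say that such a patient has no correct answer. The literal reading is available and gives the lower bound.
- **No section plans to use Q5 to corroborate Criterion 3.** A reader might say that the survey fails in that role, but the protocol assigns it patient experience and perceptions of care.
- **The loss under *both* rests on independence.** If goals are always set within a plan discussion, the strict reading loses nothing. The *either* reading then shows none of the change, and no evidence says which reading respondents use.
- **The survey is imprecise anyway.** For 40% versus 60% with 60 independent patients per round, the 95% half-width is 1.96 × √[(0.24 + 0.24)/60] = about 17.5 points. The 4-point loss under *both* (20 to 16) is small beside that; the 16-point loss under *either* (20 to 4) is not.

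Other items also join two actions, for example Q3: "Did your doctor explain how to monitor blood sugar and what to do in case of high/low readings". A reader might extend the point to Q3 and Q4. No consequence can be shown for them, and Q4 pairs the same two topics as audit Criterion 5, so splitting it would weaken that match.

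The statement that the tool was validated does not answer the point about Q5, because one answer to a two-act question cannot be separated afterwards.

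**Conclusion.** The point holds for Q5 alone, as a cheap improvement to the patient survey. As printed, Q5 cannot isolate patient-reported HbA1c goal-setting, either at baseline for the action plan or in the before-after comparison.

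The size depends on assumptions that the documents cannot settle. For a true 20-point rise in goal-setting with plan discussion at 80%, Q5 would record 16 to 20 points under *both* and 0 to 4 points under *either*, as overlap goes from independent to nested. Q5 can also rise when goal-setting has not changed. All rates are assumed, and yes/no coding is inferred.

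The record audit and Criterion 3 are untouched. The finding does not mean that the study misses goal-setting or that the other survey items need rewording.

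**What to change.** Before the baseline calls, do one of the following:

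1. **Preferred.** Keep Q5 exactly as validated and add one item that asks only whether the doctor set a target for HbA1c.
2. **Alternative.** Split Q5 into a goal item and a treatment-plan item.

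Use the same version in both rounds, report the goal item as its own percentage, and show it beside Criterion 3. Leave Q3 and Q4 as they are.

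The cost is one extra question in a six-item call. The first option leaves the validated wording intact; the second departs from it slightly. The change has to precede baseline, because answers to the joint question cannot be divided later and an item added afterwards would have no baseline value.

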### Intervention and follow-up

Following the initial cross-sectional analysis, identified gaps in care quality and patient satisfaction will inform the development of a comprehensive action plan. This plan will be implemented across all participating health centers to address the deficiencies and enhance service delivery. The intervention will be embedded into standard auditing procedures to ensure continuous quality improvement.

The intervention phase will last approximately 8–9 months. Afterward, a second round of data collection will be conducted using the same methodology and variables to ensure consistency and enable direct comparison. This approach will support the evaluation of changes in clinical performance and patient experience before and after the intervention *(see*
Fig 1
*for the study flow chart).*

**Fig 1 pone.0313664.g001:**
[figure not shown]
ICAE-DM CARE STUDY flow chart (Author’s own creation).

### Analytical plan

Data will be extracted from the electronic health record system at two separate points: one time at a point before the intervention and the other time at a point after the implementation of the intervention. Excel will be used to collect and organize the data. PivotTables will be used to determine the frequency of cases across variables. Excel will be further used to produce histograms and other figures.

Study outcome variables will be assessed using independent tests like Chi square or t test to compare between the two groups. For satisfaction, we will do it frequently by percentage P=(F/T) *100.

The statistical analysis will be performed using STATA 15.1 (College Station, TX, USA). A Wilcoxon sign rank test will be used to find the mean difference between the pre- and post-assessment. P < 0.05 will be considered statistically significant. A logical model of protocol presented in Fig 2.

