### Study population

The study population includes adult patients (≥ 18 years) who are non-pregnant and have attended PHCCs for the management of type 2 diabetes within the past two years. Patients can be newly diagnosed or on follow-up.

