### Data collection procedures

Data variables pertinent to the study objectives will be retrieved from the PHCC EMR system, including demographic information, diagnostic details, clinical encounters, and healthcare utilization patterns.

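### Separately drawn pre and post samples, with no control group, are compared by unadjusted tests, so a change in measured patient mix would be read as an audit effect

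*Protocol article*

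**What the plan says.** The Analytical plan names the comparison of the two rounds: "Study outcome variables will be assessed using independent tests like Chi square or t test to compare between the two groups". The only other test named takes no covariates either: "A Wilcoxon sign rank test will be used to find the mean difference between the pre- and post-assessment". The significance rule is "P < 0.05 will be considered statistically significant". No regression, stratified analysis or comparison of patient characteristics between rounds is described.

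Sample selection has records chosen at baseline and again after the intervention, "with 450 cases reviewed at each stage to facilitate a comparative analysis of diabetes-related encounters over the preceding three months". On the method it says: "A stratified simple random sampling method will be employed to select representative samples for both the cross-sectional and cohort components of the study". The strata are not named. After introducing the 60-patient satisfaction subset, the same section adds: "The randomization process will be independently applied at both time points to ensure comparability and minimize selection bias". Evaluation of audit impact makes a similar claim, covering chart reviews as well as surveys: using the same tools makes the two data points comparable.

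Study population allows a mixed group: "Patients can be newly diagnosed or on follow-up". Medical record review, by contrast, says the review concentrates on newly diagnosed patients. Data collection procedures lists the variables to be retrieved, "including demographic information, diagnostic details, clinical encounters, and healthcare utilization patterns", so the material for an adjusted comparison is already to be collected.

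**The concern.** Nobody is randomised to a round. Drawing at random from the patients eligible at each time protects against selective picking within a round. It does nothing about a real change in who is eligible between rounds. If the later sample is older, has a different sex balance or contains more newly diagnosed patients, and compliance with a criterion differs by that characteristic, the raw percentages move even when care has not changed. An unadjusted chi-square or t test cannot separate the two explanations.

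This matters because the protocol treats the before–after difference as evidence on the audit and as a basis for scaling up, and there is no control group in which a drift in mix would show. Wording that presents the rounds as comparable by construction invites readers to dismiss this explanation. The point concerns patient composition only. It is separate from background trends in care, from clustering by centre, and from whether a signed-rank test suits separate samples.

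**Working it through.** **1. The plan's own figure.** Sample selection gives a 5% margin, 95% confidence and a 50% proportion. n = 1.96² × 0.25 / 0.05² = 384.1, so 385. Reaching 450 needs an allowance of 1 − 385/450 = 14.4%. The allowance is not stated, so 450 is compatible with its inputs but not fully reproducible. Nothing below depends on how 450 was reached.

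**2. Precision of the comparison.** Inputs: 450 records per round and the 0.05 threshold (Analytical plan; two-sided assumed, as sidedness is not stated). Compliance near 50% is an assumption.
- SE of the difference = √(2 × 0.25 / 450) = 0.0333, or 3.33 points.
- Difference detectable with 80% power = (1.96 + 0.84) × 3.33 = 9.3 points.

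**3. False difference from mix.** For a two-level characteristic, false difference d = (change in its share between rounds) × (compliance gap between its levels). The false-positive rate with no true effect is Φ(d/SE − 1.96) + Φ(−d/SE − 1.96). Every shift and gap below is assumed.

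| Change in share | Compliance gap | d | d/SE | False-positive rate |
|---|---|---|---|---|
| 0 points | any | 0 points | 0 | 5.0% |
| 10 points | 20 points | 2 points | 0.6 | 9.2% |
| 10 points | 30 points | 3 points | 0.9 | 14.7% |
| 10 points | 40 points | 4 points | 1.2 | 22.4% |
| 15 points | 40 points | 6 points | 1.8 | 43.7% |

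A false difference of 3 to 6 points is about one third to two thirds of the detectable 9.3 points (3/9.3 = 0.32; 6/9.3 = 0.65).

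**4. Check by simulation.** There were 20,000 runs per setting, 450 per round and no true effect. The baseline share of the higher-compliance group was set at 30%.
- With a 10-point shift and compliance of 80% versus 50%, the crude test rejected in 15.5% of runs. A Cochran-Mantel-Haenszel test stratified on the characteristic rejected in 5.0%.
- Over shifts of 5–20 points and gaps of 10–40 points, d ran from 0.5 to 8 points. Crude rejection ran from about 5% to about 68%, while the stratified test stayed at 4.8%–5.2%.
- With no shift, both tests held about 5%.

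**5. Which characteristics.** Age and sex apply under either description of the population. Newly diagnosed versus follow-up status applies only if Study population, rather than Medical record review, defines who is reviewed. For criteria that apply to a subgroup (cardiovascular risk assessment from age 40, TSH in some women), the denominator is below 450. The SE is then larger, and the same d gives a lower false-positive rate than in the table.

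**The case against.** The strongest reply is that the shifts are assumed and may be small. Both rounds cover all 31 centres, with the same criteria and variables. Eligibility looks back two years while the intervention lasts 8–9 months, so the eligible populations probably overlap a good deal and age and sex may hardly move. That stands: a risk is shown, not a known bias.

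The larger shifts in the table are easiest to imagine for newly diagnosed status. If Medical record review governs and only newly diagnosed patients are audited, that route closes. This also stands, and leaves age and sex.

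Stratified draws could balance the rounds on the strata if the same strata are used each time. The strata are unnamed and do not enter the analysis, so this limits the concern without removing it.

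It can also be said that covariate lists belong in an analysis plan. That is fair for the details. But the article does not leave the method open: it names tests that take no covariates, and the word introducing them as examples does not point to adjustment.

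Some stronger inferences are tempting but not supported.
- A reader might take the sentence on independent draws as a claim about the 450 records. It directly follows the satisfaction subset; the claim that reaches chart reviews is the one in Evaluation of audit impact.
- A reader might think the age and sex conditions in Table 1 themselves create bias. Scored among applicable patients, they first change the denominator. Bias arises only if compliance also varies within that group.
- A reader might expect adjustment to bring a gain in power. The documents give no correlation between these characteristics and compliance, so no gain can be claimed.

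**Conclusion.** The point holds as a weakness of the stated analysis. The protocol fixes covariate-free tests for two separately drawn samples without a control group, although it plans to extract characteristics that would allow adjustment. Any change in measured mix that is related to compliance would be reported as an audit effect.

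The size is unknown. The 9%–44% range rests on assumed false differences of 2–6 points, compliance near 50%, 450 records per round and a two-sided 5% test. Separate samples means separate draws; a few patients may appear in both.

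A reader might infer that the study's result will be biased, or that adjustment would make the before–after difference causal. Neither follows. With no shift there is no bias. Adjustment removes only the part explained by measured characteristics. Secular trend remains, and so does selection through charting: eligibility depends on a documented diagnosis and on encounter content, and documentation is what the intervention sets out to change.

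**What to change.** 1. In the Analytical plan, make the main comparison for each Table 1 criterion, scored among the patients to whom it applies, a logistic (or linear) regression in STATA with round as the effect of interest.
2. Adjust for age, sex and the sampling strata, and for newly diagnosed versus follow-up status if both groups are reviewed. Do not adjust for encounter counts accrued during the intervention: referrals and follow-up tests can change them, and adjustment could remove part of a true effect.
3. Report the standardised difference between rounds with a 95% CI. Keep the raw percentages as description, and tabulate these characteristics by round.
4. In Sample selection, say that independent draws make each sample representative of its own time point, and amend the similar wording in Evaluation of audit impact.
5. State that the adjustment covers measured mix only, not secular trend or charting-driven eligibility, and make no claim of added power.

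The cost is a few lines of text and one regression per criterion on data already planned for extraction, with no further records. The drawbacks are that missing covariates need handling and adjusted differences are slightly less simple to present than raw percentages.

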The findings from this baseline assessment are used to identify deficiencies in clinical practice. Root cause analysis using tools such as fishbone diagrams, process mapping, and SWOT analysis is then conducted to tailor quality improvement (QI) interventions to the context [14,15]. The action plans are implemented collaboratively by a multidisciplinary team, comprising the clinical effectiveness unit, clinical operations, information systems (CIS), and the designated clinical audit champions at each health center.

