### Evaluation of audit impact

The effectiveness of the clinical audit was assessed across two domains: clinical care delivery and documentation practices. Improvements in risk assessment documentation, appropriate referrals, lab test completion, and patient education were key outcome indicators. In centers where outcomes were not achieved, qualitative insights revealed constraints such as staff turnover, limited training continuity, and EMR documentation challenges as contributing factors.

The post-intervention phase, scheduled 8–9 months after implementation, mirrors the baseline assessment in design and sample size. The use of consistent tools—open chart reviews and structured surveys ensures comparability between the two data points.

Final comparative analysis will assess the extent of change in care quality indicators and documentation standards following the audit. Where meaningful improvements are found, the results will serve as a basis for scaling similar QI strategies in other primary care settings. Where improvements are minimal, the study will inform refinements in implementation strategies, emphasizing adaptability in quality improvement processes.

This protocol offers a replicable, resource-sensitive model of continuous quality improvement in chronic disease care. Its structured, scalable methodology—rooted in evidence, stakeholder involvement, and iterative evaluation—contributes meaningfully to advancing primary care practices globally.

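### The before-after tests treat the two rounds as independent simple random samples of 450 and ignore the strata, the matched 31 centres and centre-specific change

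*Protocol article*

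**What the plan says.** Under Sample selection the article states: "A stratified simple random sampling method will be employed to select representative samples for both the cross-sectional and cohort components of the study". It does not name the strata or the allocation. For the audit, "a total of 450 patient records will be randomly selected from the medical records department across 31 health centers", and this is done twice, "with 450 cases reviewed at each stage to facilitate a comparative analysis". The basis for 450 is a precision calculation: "This sample size was calculated based on a 5% margin of error, a 95% confidence interval, and an assumed response distribution of 50" per cent, plus an allowance for non-response whose size is not given. No design effect is mentioned.

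Study settings includes all 31 centres, and Intervention and follow-up applies the same methodology in the second round, so every centre appears in both rounds. The action plan is rolled out in all centres by a team that includes "the designated clinical audit champions at each health center". The section on audit champions lets them make changes locally with the centre manager, within the approved plan.

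The Analytical plan then fixes the comparison: "Study outcome variables will be assessed using independent tests like Chi square or t test to compare between the two groups", judged at P < 0.05. It names no stratum, centre term, weight, clustered standard error or mixed model. It also names a Wilcoxon signed-rank test, without saying what the pairs are.

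**The concern.** Records from one centre share clinicians, habits and documentation practice. Three features of the design therefore bear on the variance of the before-after difference, and the named tests use none of them.

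- Stable differences between centres cancel, because each centre is its own control. Ignoring this makes the test conservative.
- Change that differs between centres adds variance. Ignoring this makes the test anti-conservative when the aim is to generalise to other centres.
- If the strata are centres and allocation is not proportional to their size, unweighted percentages may not represent the PHCC-wide rate.

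The article itself allows for uneven response. Under Evaluation of audit impact it writes: "In centers where outcomes were not achieved, qualitative insights revealed constraints such as staff turnover". The same section makes the final comparison the basis for scaling the strategy to other settings, so a p-value that is too small could support an unwarranted roll-out.

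**Working it through.** **Plan's own figure.** With z = 1.96, p = 0.5 and margin 0.05: n = 1.96² × 0.25 / 0.05² = 384.1, so 385. Reaching 450 needs an allowance of 1 − 385/450 = 14.4%. The allowance is not stated, so 450 is consistent with the inputs but cannot be reproduced exactly. The calculation has no term for centre.

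**Inputs.** From the article: 450 records per round, 31 centres, the same centres in both rounds, threshold 0.05. Assumed: even allocation, so m = 450/31 = 14.5 records per centre and round; a two-sided test; ICC 0.02 to 0.10; CAC 1, 0.8 and 0.5. CAC is the correlation of a centre's level between rounds; CAC 1 means that centres differ but all change alike.

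**Variance.** Relative to two independent simple random samples, the before-after difference has variance factor

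F = (1 − ICC) + m × ICC × (1 − CAC).

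Example at ICC 0.05, CAC 0.5: F = 0.95 + 14.5 × 0.05 × 0.5 = 1.31.

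**True size of the nominal 5% test** = 2 × [1 − Φ(1.96/√F)]. Simulation results are in brackets: 31 centres with 14 or 15 records, 40,000 runs, pooled two-proportion z test, which equals the uncorrected chi-square test.

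| ICC | CAC 1 | CAC 0.8 | CAC 0.5 |
|---|---|---|---|
| 0.02 | F 0.980; 4.8% (4.6%) | F 1.038; 5.4% (5.5%) | F 1.125; 6.5% (6.4%) |
| 0.05 | F 0.950; 4.4% (4.4%) | F 1.095; 6.1% (6.1%) | F 1.313; 8.7% (8.7%) |
| 0.10 | F 0.900; 3.9% (3.8%) | F 1.190; 7.2% (7.2%) | F 1.626; 12.4% (12.2%) |

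At ICC 0.01 the size is only 4.9% to 5.7% over the same CAC values.

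**Break-even.** F = 1 when m × (1 − CAC) = 1, that is CAC = 1 − 31/450 = 0.93, whatever the ICC. Near that value the planned test is correctly sized.

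**Power, as an illustration.** For 50% versus 60% compliance (not figures from the article), 450 per round give 85.6% power if records are independent, about 82% at F = 1.095 and about 75% at F = 1.31.

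**Target of inference.** If the target is the average change in these 31 centres only, centre-specific change is part of what is estimated. The error variance then keeps only the within-centre part, F ≈ 1 − ICC = 0.90 to 0.98, and the planned test has size of about 4-5%, given allocation in proportion to centre size. The larger values in the table apply when the centres stand for others.

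**The case against.** The strongest reply is that all 31 centres are included, not sampled. For the change in these centres, the test is valid or mildly conservative. This stands for that narrow target. But the Introduction calls the method replicable in other primary care settings, Evaluation of audit impact speaks of scaling it elsewhere, and the Conclusion offers it as a model worldwide. For that aim, variation between centres in response belongs in the error.

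A second reply is that ICC and CAC are assumed and the effect can be small. This also stands, and it limits what can be said about size. Uneven response is plausible, not certain: there is one approved plan for all centres.

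A third is that such detail belongs in a statistical analysis plan. The article does more than leave the method open, however: it names independent tests, which do not fit the sampling that it describes. The signed-rank test would come close to a remedy if its pairs were centres, but the article does not say so.

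Some stronger readings are tempting, and the document does not support them.

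- A reader might infer that all 900 records are treated as one sample. The test compares two groups of 450.
- A reader might infer that the test is wrong whatever the correlations. It is about right near CAC 0.93.
- A reader might apply the usual factor 1 + (m − 1) × ICC, which is 1.68 at ICC 0.05. That is for a single round and overstates the effect on a difference within the same centres.
- A reader might infer that single centres will be classified on 14 or 15 records. The remark on centres concerns qualitative barriers and sets no statistical rule.
- A reader might infer that unadjusted age and sex invalidate the p-value. Chance differences between two random samples are already in the sampling error.

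**Conclusion.** The point holds: the named tests do not match the stated design, and nothing else in the article accounts for centre. It is a moderate fault of analysis choice that should be corrected. It does not show that a positive result would be false.

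For generalisation beyond the 31 centres, the true size runs from about 4% to about 12% over ICC 0.02-0.10 and CAC 0.5-1. The upper end needs both a high ICC and substantial centre-specific change. The figures rest on even allocation and on correlations that the article does not give. Confidence is high that centre is ignored, and low on the direction and size of the resulting error. The Analytical plan promises p-values only, so the same error reaches confidence intervals only if they are derived from these tests.

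**What to change.** 1. Record the health centre for every audited record. Data collection procedures lists extraction "including demographic information, diagnostic details, clinical encounters, and healthcare utilization patterns" but does not name centre.
2. State the strata and the allocation. If allocation is not proportional to centre size, weight by centre size.
3. Replace the pooled test with a before-after comparison that accounts for centre: a logistic model for each criterion with wave and centre (random intercept plus random centre-by-wave effect).
4. Some Table 1 items apply only to some patients (for example risk assessment from age 40, or the conditional laboratory tests), so few records per centre may remain and the model may not converge. There, use a size-weighted paired analysis of the 31 centre-level differences, or centre-clustered standard errors with a small-sample correction. In a simulation with 4,000 replicates over ICC 0.05 to 0.20, an unweighted paired test on the 31 differences held its size at 4.4% to 5.3%. Weighting keeps the target at the PHCC-wide change, whereas equal weights would estimate the change in the average centre.
5. Report the risk difference with a 95% confidence interval, and say whether inference is to these 31 centres or beyond. Adjustment for age and sex is optional.

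The cost is revised analysis wording and one extra field in the extraction sheet. No more records are needed, and Stata, already named, fits these models. The downside is that p-values may be less favourable and intervals somewhat wider.
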